|  | | The **purpose** of this study is to test the feasibility and estimate the efficacy of an online mindfulness meditation intervention to help pregnant women with a history of depression to self-manage sleep.  **The specific aims are to:**   1. To identify the feasibility and acceptability of the Online Prenatal Trial in Mindfulness   Sleep Management (OPTIMISM) intervention to improve sleep in pregnant women at risk for  depression. Adherence to the online intervention will be assessed through rates of completion of the  educational components, participation in daily meditation activities, and completion of data collection.  Acceptability will be determined through participant feedback after program completion (satisfaction,  perceived benefits, and barriers) and usability testing of the intervention interface.   1. To estimate the efficacy of an online intervention to improve sleep and depression   symptoms in pregnant women with history of major depression. Our hypothesis is that the 6-week  mobile intervention will show significantly greater improvements in sleep quality and depression  symptoms compared to education control. Using a randomized study design, this pilot study will  provide preliminary estimates of intervention effect size magnitude in pregnant women on the following  outcomes:   1. The primary study outcome of global sleep quality will be measured at baseline and post-intervention and compared between the intervention and education-only control. 2. The secondary sleep and mood outcomes of actigraphy and self-reported sleep and mood will be measured at baseline and post-intervention and compared between the intervention and education-only control. 3. Exploratory measures of self-efficacy, activation, motivation, and mindfulness will be compared pre and post intervention between the intervention and education-only control. | | | | | | | | | | | | | | | | | |
| **1.6** **Study design**. Provide a one-sentence description of the general study design and/or type of methodology. | | | | | | | | | | | | | | | | | | | |
| *Your answer will help HSD in assigning applications to reviewers and in managing workload. Examples: a longitudinal observational study; a double-blind, placebo-controlled randomized study; ethnographic interviews; web scraping from a convenience sample of blogs; medical record review; coordinating center for a multi-site study.* | | | | | | | | | | | | | | | | | | | |

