|  | T1: Baseline assessment. Once initial eligibility criteria are met based on telephone screening, participants will schedule a time to meet the PI at their home to discuss the study, answer questions, and provide written informed consent. After receiving consent, verbal and written instructions will be provided for wearing an ActiWatch (wrist actigraphic device) on the non-dominant wrist for 8 consecutive days (7 nights) and participants will commence daily online sleep diaries. A link to the online assessment on REDCap will be sent to participants by email after the home visit. Baseline assessments will include completion of self-reported questionnaires (demographics, pregnancy characteristics, height and weight [pre-pregnant and current], sleep [PSQI and PROMIS measures], and measures of self-management [self-efficacy, motivation, activation], mood [depression, anxiety, positive affect], and general health status). The estimated time to complete the online baseline assessment on REDCap is 60 minutes. After completion of the baseline assessment, eligible women will be block-randomized to receive OPTIMISM or active control. Participants will not be informed about the general content of the other online intervention. After completion of one 8 days and 7 nights of actigraphy data collection, participants will meet with a research assistant to retrieve the Actiwatch and receive instruction in the intervention or control condition. Daily diaries will continue for the duration of the study.  [figure not shown]Intervention. The OPTIMISM intervention consists of six weekly online self-directed learning modules about mindfulness meditation, sleep challenges in pregnancy, and behavioral strategies to improve sleep (Table 1). Building on experience developing mindfulness interventions for at-risk pregnant populations, the program will adapt elements of two in-person mindfulness-based interventions: Mindfulness-Based Childbirth and Parenting (MBCP) and Mindfulness-Based Therapy for Insomnia (MBTI). The emphasis of intervention activities will be the use of mindful awareness as a sleep self-management technique to increase total sleep time (TST) and sleep efficiency (SE). Intervention activities and assessments will be delivered through Research Electronic Data Capture (REDCap) and linked web-pages. Each weekly module will contain linked didactic content on sleep, pregnancy, and mindfulness meditation using interactive text and video, audio meditations (short and long versions), discussion-board for interaction with a certified Mindfulness instructor (who is not the PI) and other participants, and weekly reflective exercises. Integration of the intervention into REDCap surveys will allow automatic data capture on module completion and access to meditations. Support during daytime hours will be available through text or email communication with the mindfulness instructor. The mindfulness instructor will provide weekly feedback to participants through email about their assignments and progress toward sleep improvement. Participants will also have opportunities to ask questions and provide feedback within each module of the didactic content. Daily reminders about practicing mindfulness and/or short messages to reinforce course content will be sent by text and/or email. Each participant’s progress in the course will be monitored weekly through REDCap, which will provide ongoing feasibility data. Every day during the course participants will complete the CISSM sleep diary on REDCap, modified to include pregnancy symptoms interfering with sleep, along with daily meditation practice. The diary will help participants self-manage their sleep and monitor progress in meeting sleep-related goals. Weekly progress on sleep goals will be calculated and provided to participants by an emailed report and displayed on a dashboard on the intervention website.  Usability testing of the intervention platform and dashboard will be offered as an optional procedure to participants assigned to the intervention group. Usability testing will be scheduled at two times: early during the intervention (after orientation to the website); and during week 5 or 6. The portable Usability Lab (Noldus Information Technology, Lesburg, VA) includes an electronic tablet loaded with the application, Morae recorder software (version 3.3), and a video-camera. This portable system supports synchronous recordings of human-computer interactions, video and audio, high resolution screen capturing, and is operating system independent. We will directly observe (and audio- and video-record) users as they interact with the intervention in their homes or offices. In addition, all users will be asked to verbally describe their actions and strategies when interacting with the online intervention, “thinking aloud” about how and why they make specific choices in their interactions. These interactions include navigating within the intervention website, viewing and understanding the sleep dashboard, and completing online sleep diaries, Participants will also provide feedback on different dashboard mockup designs.  [figure not shown]Control. The education-only control (EOC) intervention (Table 2) will deliver education on sleep hygiene, pregnancy, and childbirth in a modular format. This will not include any mindfulness content or meditations, sleep scheduling (bed restriction or stimulus control recommendations), reflective exercises, or development of sleep goals. Control participants will complete CISSM sleep diaries and have access to an online discussion board limited to control group participants and an instructor/moderator. Control group participants will not receive feedback from the instructor on any changes in their sleep during the study.  T2: Post-intervention assessment. After intervention completion, participants will complete assessments online through REDCap. The estimated time to complete the baseline assessment on REDCap is 60 minutes. A research assistant will arrange to meet the participant to deliver the Actiwatches for another session of actigraphy monitoring. The participant will for wear an ActiWatch on the non-dominant wrist for 8 consecutive days (7 nights) Sleep diaries will continue through the end of T_2_ actigraphy data collection for Intervention and Control Group participants. After the actigraphy monitoring is complete the research assistant will arrange retrieval of the ActiWatch.  Table 2. Education-only control outline  Postpartum assessment. Approximately four weeks after the expected birth, participants will complete a postpartum questionnaire online through REDCap. The estimated time to complete this assessment will be 15 minutes. The participant will receive an email with a link to the online assessment. At the end of the questionnaire, information about the key differences in content between the two interventions will be provided to all participants. This will include;   - The mindfulness intervention focused on use of mindfulness meditation, sleep restriction, and stimulus control - The active control condition focused on education about sleep and strategies to improve sleep that do NOT include meditation, sleep restriction, or stimulus control.   This will conclude participant's involvement in the research study although they will be provided contact information for research study staff for any further questions or comments. | | | | | | | | | | | | | | | | | | | | | | | | | | | | | | | | | | | | | | | | | | | | | | | | | |

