|  | | | **Prescreening**  Age, gestational age, mental health history (recent diagnosis of major depression, past history of depression, other significant psychiatric illness), Patient Health Questionnaire (PHQ-9), Insomnia Severity Index (ISI), self-report of height and pre-pregnancy and current weight, and snoring frequency.  **Data collected only at baseline (T1)**  Demographic Survey – education, race/ethnicity, parity, household income, marital status, household composition, and sleep partners.  **Data collected at baseline (T1) and post-intervention (T2) assessment**  **Pregnancy health**: current height and weight, gestational age, pregnancy complications, medical and psychiatric co-morbidities, medications, and substance use.  **Pittsburgh Sleep Quality Index (PSQI)** is a 19-item survey to assess sleep quality and usual sleep habits over the previous month.  **PROMIS Sleep Related Impairment – Short Form** has 8 items related to consequences from poor sleep to daily function, on a 5-point Likert-type scale ranging from 1 (not at all) to 5 (very much).  **PROMIS Sleep Disturbance – Short Form** has 8 items related to sleep quality and difficulty falling asleep over the past 7 days, on a 5-point Likert-type scale.  **PROMIS Fatigue -- Short Form** has 8 items related to decreased energy and activity secondary to fatigue over the past 7 days. Items are scored on a 5-point Likert-type scale.  **Edinburgh Postnatal Depression Scale (EPDS)** is a 10-item self-report questionnaire that assesses symptoms of depression in the past 7 days and has been validated for use in pregnancy and postpartum.  **PROMIS Emotional Distress -- Anxiety Short Form** has 8 items on feelings related to anxiety felt over the past 7 days. Items are scored on a 5-point Likert-type scale ranging from 1 (never) to 5 (always).  **PROMIS Positive Affect – SF** has 15 items that reflect a level of pleasurable engagement with the environment, such as happiness, joy, and enthusiasm.  **SF-36** is an indicator of overall health status across vitality, physical functioning, bodily pain, general health perceptions, physical role functioning, emotional role functioning, social role functioning, and mental health..  **Patient Activation Measure** has 13 items that measures a patient’s level of activation (capacity for self-management and involvement) in health care actions and decisions.  **Index of Self-Regulation** has 9 items that measure how a person feels about taking care of themselves.  **PROMIS Self-Efficacy for Managing Emotions SF** has 4 items that measure current level of confidence in handling stress and negative emotions.  **Five Facet Mindfulness Questionnaire (FFMQ) Short Form** is a 24-item measure of mindfulness. Subscales include observing, describing, acting with awareness, nonjudging, and nonreactivity. Higher scores indicate higher levels of mindfulness. The FFMQ-SF has been validated in pregnancy.  **Sleep diaries** (collected daily from baseline through study completion)  Sleep diaries will provide subjective measurement of sleep variables such as bed/rise times, sleep onset latency (SOL), wake after sleep onset (WASO), number of awakenings (NWAK), total sleep time (TST), time in bed (TIB), and sleep efficiency (SE). Sleep diaries will also include questions on sleep schedule; caffeine, nicotine, alcohol, and medication use; frequency, type, and duration of meditation practice (Intervention group).    **Actigraphy**  Wrist actigraphy with Actiwatches (Phillips Respironics, Bend, OR) will be used to measure sleep/wake patterns at home for 8 days (7 nights) at baseline and post-intervention. Sleep variables obtained via actigraphy include sleep onset, sleep offset, sleep period time, mean activity during sleep, mean number of minutes of sleep and wake, percentage of sleep and wake within the sleep period, and number of waking episodes during the sleep period. These variables are used to derive total sleep time, percent sleep efficiency (SE, sleep time/time in bed x 100), percent wake after sleep onset (WASO, wake min/sleep time x 100), and a fragmentation index (of waking episodes/hr).  **Intervention adherence**  Intervention adherence will be measured on REDCap through completion of intervention modules, frequency of meditation practice, and frequency of completion of 8 weeks of daily sleep diary collection in pregnancy.  **Data collected only at post-intervention (T2) assessment**  Intervention acceptability will be measured with questionnaires administered at T2 using 5-point Likert-type scale items about their experiences with using the intervention web-platform and perceived benefits and challenges of the program. Open-ended qualitative questions will solicit general feedback on the intervention, and explanation of quantitative responses. Acceptability questions will focus both on the substance of the intervention as well as Internet delivery and mobile device compatibility.  **Data collected at postpartum assessment**  **Obstetric outcomes** (preterm birth, mode of delivery, NICU admission, birth weight, use of pain medications in labor, delayed discharge from hospital, and lactation. No identifiers will be collected for the infants (such as birthdate).  **Main outcomes** (Pittsburgh Sleep Quality Index and Edinburgh Postnatal Depression Scale)  **Intervention sustainability** (continued use of the intervention, satisfaction, and feedback) | | | | | | | | | | | | | | | | | | | | | | | | | | | | | | | | | | | | | | | | | | | | | | | |

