| **10.6 Un-blinding.** If this is a double-blinded or single-blinded study in which the participant and/or you do not know the group to which the participant is assigned: describe the circumstances under which un-blinding would be necessary, and to whom the un-blinded information would be provided. | | | | | | | | |
|  | | n/a | | | | | | |
| **10.7 Withdrawal of participants.** If applicable, describe the anticipated circumstances under which participants will be withdrawn from the research without their consent. Also, describe any procedures for orderly withdrawal of a participant, regardless of the reason, including whether it will involve partial withdrawal from procedures and any intervention but continued data collection or long-term follow-up. | | | | | | | | |
|  | | Participants may withdraw from the study at any time. Participants will also be asked to provide rationale behind their decision to withdraw, though they may choose not to provide rationale. The PI will ask if the participants are willing to continue with follow-up assessments (T2), but participants may choose to participate in data collection or not. | | | | | | |
| **10.8 Anticipated direct benefits to participants**. If there are any direct research-related benefits that some or all individual participants are likely to experience from taking part in the research, describe them below: | | | | | | | | |
| *Do not include benefits to society or others, and do not include subject payment (if any). Examples: medical benefits such as laboratory tests (if subjects receive the results); psychological resources made available to participants; training or education that is provided.* | | | | | | | | |
|  | | Benefits to participants include learning about their sleep patterns and strategies that may improve sleep self-management. | | | | | | |
| **10.9 Individual subjects findings.** | | | | | | | | |
|  | | **a**. Is it likely that your research will unintentionally discover a previously unknown condition such as a disease, suicidal intentions, or genetic predisposition? | | | | | | |
|  | | | **x** | **No** | |  | | |
|  | | |  | **Yes** | | 🡪 If yes, explain whether and how you would share the information with the subject. | | |
|  | | |  | | |  |  |  |
|  | | **b**. Do you plan to share the individual results of any of your study procedures or findings with the subjects – such as genetic test results, laboratory tests, etc.? | | | | | | |

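### The questionnaire items behind Aim 1's acceptability result are scheduled only at T2, so the views of women who stop the programme may be lost

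*Protocol*

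**What the plan says.** Aim 1 (Protocol 1.5) covers feasibility and acceptability of OPTIMISM. On the second it states: "Acceptability will be determined through participant feedback after program completion", listing satisfaction, benefits and barriers as the content, "and usability testing of the intervention interface".

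Section 5.2 puts the instrument under data collected at T2 and at no other time: "Intervention acceptability will be measured with questionnaires administered at T2 using 5-point Likert-type scale items". Open-ended questions go with it. Section 5.1 places T2 after the intervention is complete and describes it as online questionnaires plus a further 8 days of actigraphy. The T2 paragraph gives 60 minutes for the questionnaires, although that sentence names the baseline assessment.

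On withdrawal, section 10.7 has the investigator ask for a reason, which the woman need not give. It continues: "The PI will ask if the participants are willing to continue with follow-up assessments (T2"), and leaves the choice to her.

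Three other sources of opinion appear:

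- Usability testing, which "will be offered as an optional procedure to participants assigned to the intervention group", takes place "early during the intervention (after orientation to the website); and during week 5 or 6" (5.1).
- Feedback during the course: "Participants will also have opportunities to ask questions and provide feedback within each module of the didactic content" (5.1).
- Satisfaction and feedback in the postpartum questionnaire, listed in 5.2 under sustainability.

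**The concern.** Acceptability is half of Aim 1 in a study whose purpose is to test feasibility. The women best placed to describe barriers are those who stopped because of them, and the schedule makes their answers the easiest to lose. The items come at the end of the programme, within an assessment that a woman who withdraws is free to refuse. Disliking the programme could lead both to stopping and to not answering. Acceptability among those who answer would then be more favourable than acceptability among all women given OPTIMISM.

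An analysis plan can set a denominator or a rule for missing answers. It cannot recover answers that nobody asked for, so when and to whom the items are offered has to be settled in the protocol.

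**Working it through.** The protocol states no acceptability percentage, threshold or dropout rate, so there is no figure to reproduce. The check has two parts.

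**1. Does any other source give the same information from women who stop?**

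- *Usability testing* starts early enough to reach some women who later stop. It is optional, and 5.1 describes it as observing navigation, use of the sleep dashboard and diary completion. It is about the interface. It does not ask about satisfaction with the programme or barriers to following it.
- *Module feedback* comes only from women still opening modules, and 5.2 does not list it as acceptability data.
- *Postpartum satisfaction* is assigned to sustainability. For women who withdraw, 10.7 names only T2 as continued follow-up.
- *Withdrawal reasons* are requested, but nothing in 1.5 or 5.2 counts them towards acceptability.
- *Stopping the modules without withdrawing* is not covered by 10.7. The natural reading is that such a woman remains due for T2, but the protocol does not say so.

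None of these replaces the T2 items.

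**2. How large could the effect be?** All values here are assumptions except the 25, which is the per-group number in section 2.7. That section gives it as the maximum expected to complete; it is used here as the number randomised.

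Let n = 25 women in the OPTIMISM arm, w = number who stop, f = share of those who stop who answer at T2, pc = 85% acceptability in the others, and ps = acceptability in those who stop.

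- Observed = [(n − w)·pc + w·f·ps] / [(n − w) + w·f]
- All women = [(n − w)·pc + w·ps] / n

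Example with w = 5 and ps = 30%:

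- All women: (20 × 0.85 + 5 × 0.30) / 25 = 18.5 / 25 = 74.0%.
- Observed if none of the 5 answers: 85.0%, an overstatement of 11.0 points.
- Observed if half answer: (17 + 2.5 × 0.30) / 22.5 = 17.75 / 22.5 = 78.9%, an overstatement of 4.9 points.

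Overstatement in percentage points:

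| Women who stop | ps | None answer | Half answer | All answer |
|---|---|---|---|---|
| 3 | 60% | 3.0 | 1.4 | 0 |
| 3 | 30% | 6.6 | 3.1 | 0 |
| 5 | 60% | 5.0 | 2.2 | 0 |
| 5 | 30% | 11.0 | 4.9 | 0 |
| 8 | 60% | 8.0 | 3.2 | 0 |
| 8 | 30% | 17.6 | 7.1 | 0 |

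If ps = pc, every entry is zero.

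When nobody who stops answers, the formulas reduce to (w/n)·(pc − ps). Reading 25 as completers, so that 5 stopping means 30 randomised, gives 5/30 × 25 = 4.2 points and 5/30 × 55 = 9.2 points, in place of 5.0 and 11.0.

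**The case against.** The strongest reply is that the protocol does approach these women. Section 10.7 asks anyone who withdraws both for a reason and for T2, where the acceptability items sit. No passage restricts T2 to completers, and the timing phrase in 1.5 can be read simply as the post-intervention time point used for the other outcomes. Section 10.1 lets participants skip questions or stop a questionnaire, so T2 is not all or nothing. Aim 1 also reports rates of module completion, meditation and data completion, so dropout would be visible beside any acceptability result. Denominators and missing answers may be dealt with in an analysis plan that is not shown.

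Most of this stands, and it rules out three stronger inferences that a reader might draw:

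- *That acceptability rests on end-of-programme feedback alone.* It does not: 1.5 names usability testing in the same sentence, and one of its sessions is early.
- *That women who stop are left out by design.* They are not: 10.7 invites them.
- *That the estimate is biased upward as a matter of fact.* It is not established: the bias depends on who answers and vanishes if all do.

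What the reply does not meet is the practical gap. No short route to the items is offered to a woman who has had enough. Under section 4.4 the second $50 card follows completion of both the T2 assessment and actigraphy, and no payment is stated for answering the acceptability items alone. Adherence rates show that women stopped; they do not show what they thought of the programme.

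**Conclusion.** The point holds as a risk built into the data collection. The satisfaction, benefit and barrier items are requested only at T2. Women who withdraw may decline T2 and may decline to give a reason, and no other listed source supplies the same information. Acceptability will be overstated if women who stop because they dislike the programme answer less often than the others.

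The size cannot be derived from the documents. Under the assumed values above it runs from zero, if all who stop answer or hold similar views, to 17.6 points, if 8 of 25 stop, 30% of them find the programme acceptable and none answers. The conclusion rests on two assumptions that the protocol neither states nor excludes: that stopping is partly due to low acceptability, and that non-response at T2 is more common among women who stop.

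**What to change.** - **Section 1.5:** replace the timing phrase so that the existing acceptability items are sought from every woman randomised to OPTIMISM, whether or not she completes the modules.
- **Section 5.2:** collect the items at T2, or on a short stand-alone REDCap form when a woman stops the modules or withdraws, without requiring the rest of T2. List recorded withdrawal reasons as acceptability data.
- **Section 10.7:** say that the short form is offered at withdrawal, and add the woman who stops the modules without withdrawing.
- **Reporting:** give results by completion status, with the number answering out of all women randomised to OPTIMISM. The control arm does not belong in this denominator, because Aim 1 concerns OPTIMISM.

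The cost is one form that reuses existing items and about a sentence in each of the three sections. The form is voluntary, so some women will still decline and selective non-response will be reduced but not removed. The reported figure may be less favourable.

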| **4.3 Relationship with participant population**. Do any members of the study team have an existing relationship with the study population(s)? | | | | | | | | | | | | | | | | | |
| *Examples: a study team member may have a dual role with the study population (for example, being their clinical care provider, teacher, laboratory directory or tribal leader in addition to recruiting them for his/her research).* | | | | | | | | | | | | | | | | | |
|  | | | | **x** | | | | **No** |  | | | | | | | | |
|  | | | |  | | | | **Yes** | 🡪 If yes, describe the nature of the relationship. | | | | | | | | |
|  | | | | |  | | |  | | | |  | | | | | |
| **4.4 Payment to participants**. Describe any payment you will provide, including:   - The total amount/value - Whether payment will be “pro-rated” so that participants who are unable to complete the research may still receive some part of the payment | | | | | | | | | | | | | | | | | |
| *The IRB expects the consent process or study information provided to the subjects to include information about the number and amount of payments, and especially the time when subjects can expect to receive payment. One of the most frequent complaints received by HSD is from subjects who expected to receive cash or a check on the day that they completed a study and who were angry or disappointed when payment took 6-8 weeks to reach them.*  *Do not include a description of any expenses that will be reimbursed.* | | | | | | | | | | | | | | | | | |
|  | Participants who agree to participate in the study will receive a monetary incentive of up to $100 (in retail gift cards). The incentives will be divided into two portions such that:   - $50 gift card will be given after the completion of the baseline assessment and actigraphy, at the time point when research staff conduct a home visit to explain the procedures for group assignment (intervention or control) - $50 gift card will be given after completion of the post-intervention assessment and actigraphy, either in-person when retrieving actigraphy equipment or by mail. | | | | | | | | | | | | | | | | |
| **4.5 Non-monetary compensation**. Describe any non-monetary compensation you will provide. Example: extra credit for students; a toy for a child. If you will be offering class credit to students, you must provide (and describe) an alternate way for the students to earn the extra credit without participating in your research. | | | | | | | | | | | | | | | | | |

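### The randomisation trigger in section 5.1 is not tied to the end of baseline actigraphy, so women can be randomised, and lost, before the watch week is complete

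*Protocol*

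**What the plan says.** Section 5.1, under the T1 heading, gives events in this order. At the consent visit women receive the Actiwatch instructions for 8 days (7 nights) and begin daily diaries. Then: "A link to the online assessment on REDCap will be sent to participants by email after the home visit". The content is described as follows: "Baseline assessments will include completion of self-reported questionnaires", with a list that does not mention actigraphy. The next sentence reads: "The estimated time to complete the online baseline assessment on REDCap is 60 minutes". Then comes the trigger: "After completion of the baseline assessment, eligible women will be block-randomized to receive OPTIMISM or active control". Only after that does the text reach the end of the watch week: "After completion of one 8 days and 7 nights of actigraphy data collection, participants will meet with a research assistant to retrieve the Actiwatch". The allocated condition is taught at that same meeting.

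Section 4.4 (payment) names two things: "50 gift card will be given after the completion of the baseline assessment and actigraphy". It places the home visit that explains group assignment after both. Its second payment likewise separates the post-intervention assessment from actigraphy.

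Section 1.5 makes global sleep quality the primary outcome and actigraphy a secondary outcome. It lists completion of data collection among the Aim 1 adherence measures. Section 2.7 gives 25 women per group as the maximum who will complete the research.

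**The concern.** If the trigger is the questionnaire, allocation exists while the baseline of the objective sleep outcomes is still being recorded. Two things follow.

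First, a woman who stops wearing the watch or cannot be met again is already a randomised participant, although she has been taught neither condition. Her loss says something about the burden of the run-in and nothing about OPTIMISM or the education control. In a pilot whose first aim is feasibility, the two kinds of loss should be kept apart. Randomising later would keep them apart by design.

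Second, the actigraphy and diary baseline can be recorded after allocation. The protocol does not say that the assignment is withheld until the retrieval visit. Section 10.6, on un-blinding, is answered as not applicable. Section 5.1 withholds from each woman only the general content of the other programme. Section 5.2 marks the diary's meditation items as being for the intervention group. If the diary version follows the assigned arm, early randomisation could reveal the arm during the baseline week. The documents do not say whether it does.

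**Working it through.** The protocol has no figure of its own to reproduce here, so this is mainly a comparison of passages with some simple arithmetic.

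**Step 1: what the trigger refers to.**
- Section 5.1 lists the baseline assessments as self-reported questionnaires and times the online assessment at 60 minutes, immediately before the randomisation sentence.
- The T2 paragraph of 5.1 again attaches the term to a 60-minute REDCap form and then describes the watch separately.
- Section 4.4 names assessment and actigraphy as two items.
- In the other direction, the paragraph that includes the watch week is headed as the T1 baseline assessment, and section 5.2 describes actigraphy as measured at baseline.

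The nearest reading is the questionnaire. The wider reading is possible. No sentence rules out the early order.

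**Step 2: how many baseline nights can follow randomisation.** The watch week starts at the consent visit, and the questionnaire link is emailed after that visit with no deadline. Completion on day 1 leaves 7 of 7 nights to record. Completion after the last night leaves 0. The range is 0 to 7 nights.

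**Step 3: whether the intervention can start before the baseline ends.** Section 5.2 counts 8 weeks of daily diaries. Seven baseline nights + 6 × 7 = 42 intervention days + 7 post-intervention nights = 56 days, and 56 / 7 = 8 weeks. The total matches, and it fits an intervention that begins only after baseline actigraphy. It also suggests that the diary adherence measure includes the week before instruction, so women lost in that week would lower it.

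**Step 4: scale, as illustration only.** The protocol gives no loss rate, and its 25 per group are completers. For an assumed loss d in the watch week, and none afterwards, the number to randomise per arm for 25 completers is 25 / (1 − d), rounded up:

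| Assumed loss d | 25 / (1 − d) | Randomised per arm | Above 25 |
|---|---|---|---|
| 5% | 26.3 | 27 | 2 |
| 10% | 27.8 | 28 | 3 |
| 15% | 29.4 | 30 | 5 |
| 20% | 31.25 | 32 | 7 |

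On these assumptions, about 2 to 7 extra women per arm would be randomised only to replace women who never reached their condition.

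**The case against.** The strongest reply is that the order is not stated outright. The randomisation sentence drops the word online that appears in the sentence before it, the T1 heading covers the watch as well, and a list introduced by what it will include need not be complete. Section 4.4 places the explanation of group assignment after both measures. A site could follow the protocol and still randomise at the retrieval visit. This stands: the firm finding is that the wording permits early randomisation, and a reader who infers that women are certainly randomised before actigraphy ends goes beyond the text.

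Three further inferences are tempting and are not supported.

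- **That the actigraphy baseline is contaminated by the intervention.** It is not. After the watch week, "participants will meet with a research assistant to retrieve the Actiwatch and receive instruction in the intervention or control condition". The baseline precedes the intervention on either reading.
- **That the primary comparison is affected.** The PSQI, and also the EPDS, are among the online questionnaires, which are finished before randomisation on either reading.
- **That staff or participants know the allocation during the watch week.** No passage says so. Actigraphy is recorded by a device and diaries are completed online by the woman herself, so a route from staff knowledge to the data is not shown. The supportable criticism is narrower: concealment until the visit is not stated.

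It is also fair that abandoning data collection is itself a feasibility result under Aim 1, and that losses before either condition is taught should be unrelated to arm unless allocation is known. Neither point removes the difficulty that run-in loss and intervention drop-out would be counted together among randomised women.

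**Conclusion.** The point holds as a moderate defect of sequence. As worded, section 5.1 allows block-randomisation once the questionnaires are complete, with between 0 and 7 of the 7 baseline actigraphy and diary nights still to come. What is at stake is the interpretation of the Aim 1 completion and adherence rates, and the pre-allocation status of the secondary actigraphy and diary baseline. The primary outcome's baseline is intact, and all baselines are pre-intervention.

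The conclusion rests on taking the trigger to mean the questionnaires, which is the natural but not the only reading. The number of women affected cannot be stated. A reader might take one woman as 4% of an arm (1/25) and apply an assumed loss to 25, but section 2.7 defines 25 as completers, so early losses do not come out of that number. The table above shows only how the randomised total would move under assumed rates.

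**What to change.** Reword the sentence in section 5.1 so that randomisation takes place once both the online questionnaires and the 7-night baseline actigraphy are complete, at or immediately before the existing visit at which the Actiwatch is collected and the condition is taught. Use the same terms in section 4.4, so that the baseline assessment either clearly includes or clearly excludes actigraphy in both places.

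If the sponsor has a reason to randomise earlier, the protocol should instead state that allocation stays concealed from participants and staff until that visit. It should also state that all randomised women are counted, with losses before instruction reported separately from later ones.

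The preferred change costs a sentence of wording and a later point of allocation. The visit, the staff and the payment point already exist, and no participants are added. The protocol does not say what system performs the randomisation, so the sponsor should confirm that an allocation can be obtained at or just before that visit. The timing cannot be corrected for women already randomised, so it should be settled before enrolment.
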